# Introduction

Atrial fibrillation (AF) is the new cardiac epidemic in the Western countries[1–3]. It can be a fatal cardiac disease especially due to the risk of stroke where 70% of the patients will be either disabled or die[4,5]. Consequences are huge both for each patient individually and for the health care economy[6].

While the incidence of ischemic heart disease has decreased, the incidence of AF has increased and is expected to increase even further, primarily due to improved treatment of other cardiac diseases and a higher life expectancy[7,8]. Besides a higher risk of hospital admissions due to AF, many patients have symptoms from AF on daily basis and feel anxious to participate in physical exercise. This affects their normal social behavior and impairs the quality of life[9].

Medical treatment is complex and can be hazardous due to side effects. Several studies of antiarrhythmic treatment have been interrupted due to severe side effects, the latest in 2011[10]. Therefore, medical treatment still requires individual assessment and close monitoring of the patient. Radio frequency ablation is only possible for a minority of AF patients and is associated with a risk of complications[11].

So far, we only have limited knowledge about the effect of physical exercise on AF. Long-term endurance exercise increases the risk of AF in time due to dilatation of the cardiac chambers[12,13]. However, moderate physical exercise prevents premature death and other life style diseases associated with an increased risk of AF (coronary artery disease, obesity, hypertension)[14–19]. The effect of physical exercise on early stages of AF is unknown and many patients are afraid of provoking episodes of AF or cardiac arrest when exercising.

Previously, our research team and a Norwegian research team have studied the effect of physical exercise in patients with permanent AF and found an improvement in exercise capacity and quality of life[20,21]. Based on these experiences, we now want to study the effect of physical exercise in an early stage of the disease.

The pathophysiological mechanisms for AF are also unclear. Studies of cardiac tissue samples show possible cardiac fibrosis in patients with AF. It is difficult though, to conduct these invasive studies, but it is possible in blood samples to assess markers of fibrosis reflecting atrial fibrosis[22–24]. Therefore, we have conducted a pilot study of the association between markers of fibrosis and AF. Our study showed that stromal derived factor (SDF)-1α, which recruits stem cells from the bone marrow to the heart, was significantly increased in patients with permanent AF compared to patients with paroxysmal AF. Moreover, the concentration of clusterin (a marker of biological aging) was increased in patients with AF compared to healthy controls. Cardiac fibrosis, concomitant heart failure and biological aging affects the risk of developing permanent AF and complications as stroke or death[25,26].

We also study the association between telomere length and AF. Telomere length and telomerase activity are specific genetic markers. Telomeres shorten in time and lose the ability of cell division, but telomerase can delay this process. A short telomere length is associated with coronary artery disease and heart failure, but so far no studies have been conducted regarding AF. In this trial, we study the effect of physical exercise on telomere length and telomerase activity, and whether short telomere length predicts the effect of physical exercise.

We expect to assess several outcomes due to the presence of AF in many clinical areas. The study is designed as a randomized interventional trial including patients with paroxysmal or persistent AF documented on an electrocardiogram. Patients will be allocated randomly to either low or high intensity physical exercise. In this design with two active arms we want to prevent a passive control group from exercising without our knowledge.

We hope to show that physical exercise can be used additionally to the regular medical treatment of arrhythmia.

# Study objectives

1. effect of physical exercise on risk of AF measured on daily electrocardiogram (Zenicor®) during the exercise intervention
2. effect of physical exercise on hospital admissions during one year after the intervention
3. effect of physical exercise on quality of life measured before and after the exercise intervention (SF36 and EHRA-classification)
4. effects of physical exercise on physical capacity measured by 6 Minute Walk Test and on ergometer bike
5. effect of physical exercise on the cardiac work load measured on echocardiography, 24-hour heart rate and rhythm, and blood pressure
6. the predictive value of telomere length, telomerase activity, copeptin and fibrosis markers on exercise effect

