# Hypotheses

1. high intensity physical exercise reduces burden of AF by 20% (number of AF-episodes, time to first episode)
2. high intensity physical exercise reduces hospital admissions by 20%
3. high intensity physical exercise improves quality of life on EHRA-classification and by 20% in minimum five out of eight parameters on SF36
4. high intensity physical exercise increases maximal physical capacity by 20%
5. high intensity physical exercise improves the cardiac work load by reducing the mean heart rate and blood pressure, and improving the diastolic function.
6. a significant association between telomere length and effect of exercise as well as increased telomerase activity after the exercise intervention.

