# Methods

The study is an assessor blinded, randomized controlled trial. Patients are randomized by simple drawing. For logistic reasons, an exercise team consists of ten patients. The letters A and B are equally distributed in 20 envelopes, and represents the physical exercise intensity. The sealed envelopes are all put into a larger envelope from where the patients will draw one envelope at randomization.

[figure not shown]
A total of 60 patients with paroxysmal/persistent AF will be included, using consecutive sampling, from the Department of Cardiology, Copenhagen University Hospital Hvidovre. After inclusion, baseline tests will be performed as follows: physical capacity measured on Six Minute Walk Test and maximal physical capacity measured on ergometer bike, Figure 1. Patient characteristics, medication, risk factors and comorbidity will be registered. Before the exercise intervention, all participants will complete a nurse-led rehabilitation program regarding AF. The patients will then be randomized to either low intensity physical exercise (50% of maximum physical exertion) or high intensity physical exercise (75-85% of maximum physical exertion).

The exercise intervention lasts 12 weeks with exercise sessions twice weekly of 60 and 90 minutes duration, respectively. They consist of cardiovascular exercise (cycling, running) and will be supervised by cardiac physiotherapists. Intensity is measured as perceived exertion on Borg 20 scale introduced at the initial sessions. The exercise sessions will be conducted at the hospital.

During the intervention and two months after the last exercise session, the patients upload an electrocardiogram (ECG) from a handheld ECG-device twice daily and in case of symptoms of AF.

One year after the intervention is completed the patients will be invited to a follow-up. During the follow-up time all hospital admissions are registered from the medical records.

At baseline and after the 12-week intervention, blood samples will be taken and stored in a bio bank for later analyses. A total of 90 mL. blood per participant will be drawn. The blood samples will be stored anonymously at minus 80 degrees Celsius for 10 years for future research.

The trial is expected to start in October 2012 with end of follow-up one year after the last exercise session.

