## Assessment of outcome

Burden of AF:

By using a handheld ECG device (Zenicor®), the patients transmits an ECG twice daily and in case of symptoms of arrhythmia. An episode of AF is defined as > 10 seconds with irregular frequency and no visible p-waves on ECG. Total number of AF-episodes and time to first AF-episode is registered.

One year after last the exercise session, all hospital admissions related to AF are registered from the medical records; recurrent AF, cardiac failure, stroke, dysregulated antithrombotic treatment or medical side effects, implantation of pacemaker, and surveillance of medical treatment.

Quality of Life:

At baseline and at 12-week follow up the quality of life is assessed using the Short Form 36 (SF36) and European Heart Rhythm Association score (EHRA-score).

Patient characteristics:

Age, gender, ethnicity, BMI, comorbidity, medication, cardiac risk profile (family history, smoking, hypertension, hypercholesterolemia, diabetes, stroke/TCI, claudicatio intermittens, daily physical activity, blood pressure and heart rate.

Physical capacity:

Physical capacity is measured on Six Minute Walk Test and assessment of efficiency on ergometer bike with continuously monitoring of blood pressure and ECG. A ST-depression on ECG is considered significant if it is depressed by 0.1 mV measured 60 ms after the QRS-complex. The ergometer test is considered complete when reaching 85% of maximal expected heart rate.

Cardiac load:

Blood pressure and heart rate are measured for 24 hours at baseline and 12-week follow up. Blood pressure will be reported as mean systolic and diastolic blood pressure during daytime and night time, respectively. Heart rate will be reported as mean, minimum and maximum heart rate, arrests, supraventricular and ventricular ectopic activity and number of AF-episodes.

Echocardiography is reported with standard estimates in accordance with national guidelines. Additionally, left atrium volume (ml/m^2^) will be assessed as well as diastolic function (e’, a’ and E/e’).

Biochemical and genetic markers:

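### As written, the hospital-admission window opens only after the 12 weeks of randomised exercise; it should run from randomisation

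*Protocol*

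**What the plan says.** Five sections of the Protocol bear on the admission window.

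- **Study objectives**, item 2: the "effect of physical exercise on hospital admissions during one year after the intervention". This is an explicit window, and it begins when the intervention ends.
- **Hypotheses**, item 2: "high intensity physical exercise reduces hospital admissions by 20" per cent. No period is given.
- **Methods**: "During the follow-up time all hospital admissions are registered from the medical records". This sentence directly follows the one on the one-year follow-up invitation. The trial ends with "end of follow-up one year after the last exercise session", so follow-up has a stated end but no stated start.
- **Assessment of outcome**: after a time reference to one year after the final session, "all hospital admissions related to AF are registered from the medical records". A list of qualifying categories follows, including recurrent AF, heart failure, stroke and pacemaker implantation.
- **Outcomes**: admissions for AF or its complications are a tertiary outcome, with no window.

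The order of events is clear from Methods. After baseline tests and the nurse-led programme, "The patients will then be randomized to either low intensity physical exercise" or to high intensity, and "The exercise intervention lasts 12 weeks with exercise sessions twice weekly". Randomisation therefore precedes the 12 weeks.

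**The concern.** A randomised comparison is protected by randomisation when counting starts at randomisation. Here the stated clock starts when the randomised treatment ends. Admissions in the weeks when the arms are actually exercising at different intensities fall outside the count.

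That matters in this trial because the Introduction says "The effect of physical exercise on early stages of AF is unknown", and it acknowledges that patients fear provoking an event by exercising. Admission for heart failure, for example, is an event that a handheld ECG cannot register. Hypothesis 2 is also worded for admissions in general. A count confined to the following year answers a narrower question than the one the hypothesis poses.

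A second, smaller difficulty is the anchor. If one year is counted from a patient's own last session, the start of the window depends on how long that patient kept attending, which is itself a post-randomisation event. The Protocol does not say whether the last attended or the last scheduled session is meant.

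**Working it through.** **Is there a figure to reproduce?** No. The Protocol gives no admission rate, expected count or power for admissions. Its sample-size section concerns ECGs with AF only.

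**Step 1: does any section restore the 12 weeks?**

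| Section | Start of admission window | Includes the 12 weeks? |
|---|---|---|
| Study objectives, item 2 | End of intervention | No |
| Hypotheses, item 2 | Not given | Not stated |
| Methods | Follow-up time, start undefined | Not stated |
| Assessment of outcome | One year after the final session: may be the window or the date of chart review | Not stated |
| Outcomes | Not given | Not stated |

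By contrast, the Outcomes section says expressly that the primary outcome (AF episodes) is counted both during and after the intervention. The Protocol names the exercise period where it wants it counted, and does not do so for admissions.

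**Step 2: share of time omitted.** Inputs: 12 weeks of intervention (Methods) and one year, or 52 weeks, afterwards (Study objectives). Assumption: exercise starts at randomisation. Any wait between the two would add to the omitted time.

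- Share = 12/(12 + 52) = 12/64 = 18.75%. In days: 84/(84 + 365) = 84/449 = 18.7%.
- For 60 patients: 60 × 12/52 = 13.8 person-years omitted, against 60 × 1 = 60 person-years kept (ignoring deaths and losses).

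**Step 3: what the omitted weeks could do (illustration only).** Assume a constant admission rate in the low-intensity arm and the hypothesised rate ratio of 0.80 in the year after exercise. Let r be the rate ratio during the 12 weeks. Counted from randomisation, the overall ratio is

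(0.80 × 1 + r × 12/52) / (1 + 12/52).

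| r in the 12 weeks | Overall ratio from randomisation | Ratio in the year-after window |
|---|---|---|
| 1.0 | 1.031/1.231 = 0.84 | 0.80 |
| 1.5 | 1.146/1.231 = 0.93 | 0.80 |
| 2.0 | 1.262/1.231 = 1.03 | 0.80 |

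The overall ratio equals 1 when r = 1 + 0.20 × 52/12 = 1.87.

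**Step 4: how many events.** Assume 30 patients per arm (60 patients, equal allocation) and 0.3 to 1.0 admissions per patient-year, a range that is not in the Protocol. The low-intensity arm would then have 30 × 0.3 × 12/52 = 2.1 to 30 × 1.0 × 12/52 = 6.9 admissions in the omitted weeks.

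**The case against.** The case against has real weight on several points.

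- **Exclusion may not be intended.** The explicit window stands in a one-line objective. Methods and Assessment of outcome can be read as a chart review made at one year that looks back over all follow-up. This stands: part of the fault is an undefined time origin. It does not remove the point, because the one section that states a window leaves the 12 weeks out and none puts them back.
- **A year-after window is a legitimate question about lasting effect.** This also stands, and is why that year should still be reported in its own right.
- **Admissions are only a tertiary outcome.** This is true, and it limits the weight of the point.

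A reader might also infer more than the Protocol supports.

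- *That the trial would miss AF provoked by high-intensity exercise.* It would not. Patients send ECGs twice daily and at symptoms throughout the 12 weeks, AF episodes in that period count in the primary outcome, and time to first episode is secondary. Death is a separate tertiary outcome with no restricted window.
- *That patients who leave during the 12 weeks never enter the count.* Admissions come from medical records, and nothing says that patients who stop exercising are dropped from the record review.
- *That registering all admissions in one section and AF-related ones in another is a contradiction.* The two fit together if all admissions are collected and the listed categories are analysed. The Protocol only needs to say so.
- *That the omitted 18.75% measures bias, or that early treatment would show up as later benefit.* The percentage is a share of time, and nothing in the Protocol supports the second claim.

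**Conclusion.** The point holds in a limited form. Read as written, the tertiary admission comparison begins about 12 weeks after randomisation and leaves out 18.75% of post-randomisation time, which contains the whole supervised intervention. Admission-level events in that period are not compared by randomised arm, and an unrestricted hypothesis about admissions is tested on a restricted window.

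The share of time rests only on the stated 12 weeks and one year, with exercise taken to start at randomisation. The ratios of 0.84 to 1.03, the break-even value of 1.87 and the 2 to 7 events rest on assumed rates and show a possible range, not a prediction. The size and direction of any bias cannot be computed from the Protocol. The change is worth making because it is cheap and removes a post-randomisation time origin. The primary outcome is not affected.

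**What to change.** 1. In Study objectives, Methods, Assessment of outcome and Outcomes, define the admission window in the same words: from randomisation to one year after the scheduled end of the 12-week intervention, for all randomised patients, whether or not they completed the sessions.
2. Report the 12-week period and the following year separately as well as combined. The year-after result is kept.
3. State that all admissions are registered, and that the AF-related categories listed under Assessment of outcome are the analysed subset.

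How unequal follow-up time enters the planned Poisson model can be left to the SAP.

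Cost: wording in four sections and reading the same medical records 12 weeks further back. No visit, test or procedure is added.

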# Hypotheses

1. high intensity physical exercise reduces burden of AF by 20% (number of AF-episodes, time to first episode)
2. high intensity physical exercise reduces hospital admissions by 20%
3. high intensity physical exercise improves quality of life on EHRA-classification and by 20% in minimum five out of eight parameters on SF36
4. high intensity physical exercise increases maximal physical capacity by 20%
5. high intensity physical exercise improves the cardiac work load by reducing the mean heart rate and blood pressure, and improving the diastolic function.
6. a significant association between telomere length and effect of exercise as well as increased telomerase activity after the exercise intervention.

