## Inclusion and exclusion criteria

Inclusion criteria:

1. Male or female aged ≥ 18 years
2. AF documented on ECG
3. Written informed consent

Exclusion criteria:

1. Significant language barrier
2. Severe illness with an expected survival less than one year
3. Permanent AF
4. Signs of significant cardiac comorbidity during initial testing requiring treatment (ischemic heart disease, severe aortic stenosis).

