# Outcomes

1. Primary outcome is number of AF-episodes during and after the exercise intervention measured on handheld ECG (Zenicor®)
2. Secondary outcomes are:
3. time to first AF-episode
4. change in maximal physical capacity measured on Six Minute Walk Test and ergometer bike
5. change in heart rate, blood pressure and cardiac load measured on echocardiography
6. change in quality of life
7. Tertiary outcomes are:
8. Number of hospital admissions with AF or complications to AF
9. Death
10. Change in biochemical markers

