# Statistical analyses

Patient characteristics and baseline data will be analyzed using descriptive statistics. Parametric data will be reported as mean and standard deviation (SD), non-parametric data as median and range. Depending on the distribution, student-t-test or non-parametric tests will be used when comparing the intervention groups.

The effect of exercise will be analyzed in several ways depending on outcome variable; burden of AF and hospital admissions are analyzed by Poisson regression analysis, survival analyses (time-to-event) using Kaplan-Meier plots and hazard regression analysis. All analyses will be adjusted for common cardiac comorbidities and reported with two-sided confidence intervals. A p-value < 0.05 is considered statistically significant.

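### Hypothesis 3 sets a 20%-in-five-of-eight SF36 target with no stated reference, unit or named scales, and it does not match the planned between-arm comparison of quality of life

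*Protocol*

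**What the plan says.** Hypotheses, item 3, states that "high intensity physical exercise improves quality of life on EHRA-classification and by 20% in minimum five out of eight parameters on SF36". Two conditions are joined: an EHRA improvement, and a 20% gain on at least five SF36 scales.

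The rest of the protocol treats quality of life more simply:

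- Assessment of outcome: "At baseline and at 12-week follow up the quality of life is assessed using the Short Form 36 (SF36) and European Heart Rhythm Association score". No score range is given.
- Outcomes: the secondary outcome is "change in quality of life", with no threshold attached.
- Statistical analyses: "Depending on the distribution, student-t-test or non-parametric tests will be used when comparing the intervention groups". This stands in the paragraph on baseline data. The next paragraph names methods only for AF burden, admissions and time-to-event outcomes, so this is the only stated method that fits SF36.
- Inclusion and exclusion criteria: the disease criterion is "AF documented on ECG". There is no minimum symptom level and no limit on SF36 scores.

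**The concern.** Item 3 is the only place where the protocol fixes what would count as a quality-of-life effect. It does so by a percentage on scales that have an upper limit, and by a count over scales that it does not name. The demand in points therefore changes with the reference level, and whichever five scales happen to move can carry the result.

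The outcome and analysis sections never take this target up. The trial report would then have two yardsticks: the counting rule in the hypothesis and the test between arms. If they point in different directions, the protocol does not say which one settles hypothesis 3.

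**Working it through.** **Inputs.** From the protocol: 20%; five of eight scales; EHRA joined by 'and'; 60 patients ("A total of 60 patients with paroxysmal/persistent AF will be included"); equal allocation ("The letters A and B are equally distributed in 20 envelopes"), taken as 30 per arm. Assumed, because the protocol does not give them: SF36 scales run from 0 to 100 with higher better, and the best EHRA class means no symptoms. The protocol states no expected score, SD or power for quality of life, so there is no figure of its own to reproduce.

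**Step 1: points needed.** For reference level R, a 20% gain needs 0.20 × R points.

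| R | Points needed | Score to reach |
|---|---|---|
| 25 | 5 | 30 |
| 50 | 10 | 60 |
| 70 | 14 | 84 |
| 80 | 16 | 96 |
| 85 | 17 | 102 (impossible) |

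The same 10-point gain meets the target from 50 and misses it from 70 (10/70 = 14.3%).

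**Step 2: the upper limit under each reading.** The target is reachable only if 1.2 × R ≤ 100, so R ≤ 100/1.2 = 83.3.

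- Change within a patient or arm: R is the baseline score; limit 83.3.
- High versus low intensity: R is the low-intensity arm's 12-week mean; limit 83.3, which is not a baseline limit.
- 20% read as 20 points: limit 100 − 20 = 80.

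Study objectives, item 3, speaks of measurement before and after the intervention, which suggests the first reading. The Sample size section frames the trial's aim as high against low intensity, which suggests the second.

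**Step 3: when the count is blocked.** If four scales lie above the limit, 8 − 4 = 4 remain, fewer than five. If three lie above it, five remain and all of them must reach the target.

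**Step 4: how often, for illustration only.** If the rule is applied per patient, the share with four or more scales above 83.3 was simulated with 100,000 patients per setting, normal scores clipped to 0-100, correlation 0.5 between scales and SD 15 to 25. All of these are assumptions.

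| Mean of each scale before clipping | Share blocked |
|---|---|
| 60 | 3-14% |
| 70 | 16-29% |
| 80 | 44-49% |

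If it is applied to arm means, nothing is blocked unless at least four of the eight means exceed 83.3.

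**Step 5: can the two yardsticks disagree?** Both examples use arm means.

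- Every scale rises from 50 to 60 in both arms. The high-intensity arm gains 10/50 = 20% on its own baseline, so the SF36 part is met, while the between-arm difference is 60 − 60 = 0.
- Every scale rises from 70 to 80 with high intensity and stays at 70 with low intensity. The gain is 14.3% against either reference, so the target is missed. The between-arm difference is 10 points. With an assumed SD of 15, the standard error is 15 × √(2/30) = 3.87 and the ratio is 10/3.87 = 2.58, beyond the two-sided 5% critical value of 2.00 on 58 degrees of freedom. With SD 20 the ratio is 10/5.16 = 1.94 and with SD 25 it is 10/6.45 = 1.55, both short of it.

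So the target can be met without a between-arm difference, and missed with a significant one if the SD is small enough.

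**Step 6: EHRA.** Patients already in the best class may enrol and, on the stated assumption, cannot improve. Read per patient, the joint condition is closed to them whatever happens on SF36. Read per arm, the distribution of classes can still improve.

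**The case against.** The strongest reply is that item 3 is a hypothesis about the expected size of effect, not a decision rule. It stands beside similar 20% figures for AF burden, admissions and physical capacity. The outcome is a change, the groups are compared by a test, and the threshold returns nowhere as an endpoint or responder definition. This stands to a large degree: no specified test uses the 20%, so the target's limit biases no specified analysis. It does not remove the point. A minimum of five out of eight is a counting rule, and anyone asked whether hypothesis 3 was confirmed has no other definition in the protocol.

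It can also be said that choosing lead scales belongs in an analysis plan that is not shown. That is fair for the detail of scoring and modelling. The point here is confined to the target that the protocol itself chose to fix.

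Two stronger readings are tempting. First, a reader might infer that many patients, or whole arms, will start too high to succeed. The protocol gives no baseline SF36 or EHRA figures, and its Introduction points the other way, describing daily symptoms, anxiety about exercise and impaired quality of life. Its exclusions do not remove comorbidity in general, since the analyses are to be adjusted for it. Second, a reader might infer that the conclusion would reflect baseline level instead of exercise intensity. The arms are randomised, so baseline levels are equal in expectation and a between-arm contrast still estimates the effect of intensity.

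**Conclusion.** The point holds as a mismatch and an under-defined target. Hypothesis 3 leaves the reference for the 20%, the unit and the deciding scales open, and it does not match the outcome and analysis stated elsewhere. Judged by its own wording, the conclusion depends on starting level as well as on exercise intensity, and it can differ from the between-arm test in either direction.

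The size is modest. The points required run from 5 at a reference of 25 to 16 at 80, with no possible success on a scale above 83.3 (above 80 if 20 points are meant). Outright failure of the count needs four or more scales above the limit, and its frequency in this trial is unknown. These limits rest on 0-100 scoring, and the EHRA remark rests on the best class meaning no symptoms; neither is stated in the protocol. Quality of life is a secondary outcome, and the primary outcome is untouched. The change is still worth making because it is nearly free.

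**What to change.** Restate hypothesis 3 as the difference between high and low intensity in absolute SF36 points at 12 weeks, adjusted for the baseline score that is already collected. Name one or two scores in advance as the test of the hypothesis, for example the physical and mental component summaries, and report the remaining scales descriptively. Report EHRA separately, as a between-arm comparison of class at 12 weeks given baseline class, and not as a condition to be met jointly with SF36. Word the quality-of-life entry under Outcomes to match.

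The cost is a rewording of two items, with the same questionnaires and visits. The 20% headline target is lost.
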